
To sum up, persistent COVID may affect the entire spectrum of COVID-19 patients, from those with a very mild acute disease to those who are seriously ill. The symptoms are heterogeneous, including fatigue, post-effort discomfort, dyspnea, cognitive deterioration, sleep disorders, anxiety and depression, muscle pain, brain fog, anosmia/dysgeusia, headache and limitation of the functional capacity, which affect the quality of life of the patients. The relationship between AS and vascular ageing is not clear. The starting hypothesis of this study states that individuals diagnosed with persistent COVID present greater alteration in the vascular structure and function, as well as worse vascular ageing, compared to the general population without a diagnosis of persistent COVID, since the vascular system of these people is subjected to complex inflammatory deregulation, which has not been studied to date.

Therefore, the main objectives of this study are: 1) to analyse vascular structure, vascular function, biomarkers of endothelial damage and ageing in Spanish adults diagnosed with persistent COVID, determining the differences between sexes; and 2) to analyse the association of the clinical symptoms, lifestyles (physical activity, diet, alcohol consumption and smoking habits), and psychological, cognitive and inflammatory factors with biomarkers of endothelial damage, vascular structure, function and ageing, determining the differences by sexes. Regarding the secondary objectives of this study, we will analyse the possible differences among individuals with persistent COVID according to whether the infection is caused by the Delta mutation or the Omicron mutation. Furthermore, in order to continue advancing in the recognition and visibility of the patients affected by persistent COVID, they will be given a voice through a focal discussion group, where we will delve into the opinions and experiences of the population to facilitate the transfer of the study to the habitual clinical practice.

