### 2.4 Statistical analysis

The data will be registered using the REDCap platform (Research Electronic Data Capture) (Harris et al., 2009; Harris et al., 2019) with a data-gathering questionnaire designed for the project. The normal distribution of the variables will be verified through the Kolmogorov-Smirnov test. The arterial stiffness variables will be standardized and expressed as Z scores to compare results with other reference populations. The analysis of the difference of means between variables of two categories will be performed through Student’s t-test or Mann-Whitney U-test, depending on each case, whereas the qualitative variables will be analysed through X^2^ test. To analyse the relationship between qualitative variables of more than two categories and quantitative variables, an analysis of variance (ANOVA) will be conducted, and a Bonferroni’s test will be performed for the post hoc analyses. The Kruskal-Wallis test will be applied in those cases in which the variables do not show a normal distribution. The analysis of covariance (ANCOVA) will be carried out to control for the variables that can be affected by the results as confounding factors. The relationship among quantitative variables will be analysed using Pearson’s or Spearman’s correlation, depending on each case. In the multivariate analysis, we will use multiple linear regression and logistic regression analyses, with the necessary adjustments according to the type of variables analysed. All variables will be analysed disaggregated by sex, and, whenever applicable, the differences will be analysed from a gender perspective, considering the known influence of gender on many pathologies, particularly cardiovascular and cerebrovascular diseases. The data will be analysed using the SPSS v28.0 statistical package for Windows (IBM, Armonk, New York: IBM Corp). Statistical significance will be set at p < 0.05.

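### Sex differences in associations are part of a main objective, but no method named in section 2.4 tests whether an association differs between men and women

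*Protocol article*

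**What the plan says.** The Introduction opens its list of aims with "Therefore, the main objectives of this study are". The second main objective concerns the association of clinical symptoms, lifestyles, and psychological, cognitive and inflammatory factors "with biomarkers of endothelial damage, vascular structure, function and ageing, determining the differences by sexes". Section 4 (Brief summary) repeats the aim. A difference between the sexes in an association is therefore part of a main question.

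Section 2.4 (Statistical analysis) deals with sex in one sentence. It begins "All variables will be analysed disaggregated by sex" and goes on to say that "whenever applicable, the differences will be analysed from a gender perspective".

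The other methods in that section that could bear on the question are:

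- For two groups: "The analysis of the difference of means between variables of two categories will be performed through Student’s t-test or Mann-Whitney U-test", with a chi-square test for qualitative variables.
- For associations: "The relationship among quantitative variables will be analysed using Pearson’s or Spearman’s correlation, depending on each case".
- For multivariable work: "we will use multiple linear regression and logistic regression analyses, with the necessary adjustments according to the type of variables analysed".
- As the decision threshold: "Statistical significance will be set at p < 0.05".

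**The concern.** Whether an association differs between men and women is a question about a contrast: the slope or correlation in one sex minus that in the other. Splitting the data gives two estimates and two p-values, but no estimate of the contrast and no measure of its uncertainty. The commitment to analyse differences from a gender perspective shows intent but names no test, model term or contrast. The t-test, Mann-Whitney and chi-square tests can show that men and women differ in level, for example in mean cfPWV. They cannot show that fatigue or physical activity relates to cfPWV differently in the two sexes.

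With separate results and one threshold of 0.05, the natural reading of the output is that a factor matters in the sex where it is significant and not in the other. That reading confuses a difference in significance with a significant difference. Objective 2 crosses many factors with several vascular measures and 11 biomarkers, so there would be many chances to make it.

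**Working it through.** **The plan's own figure.** Section 2.2 gives a difference of 0.35 m/s in cfPWV, SD 2.1, two-sided alpha 0.05 and beta below 0.2. As a comparison with a fixed reference mean, n = (2.1 × (1.960 + 0.842) / 0.35)² = 282.6, so 283, as stated. The planned 300 therefore rests on a contrast with an external population. No sex contrast entered the sample size.

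**Inputs for the check.** From the document: N = 300 and significance at 0.05. Assumed, because the document gives neither: the split by sex (150/150, 200/100 and 225/75, the larger group taken as women) and a true correlation r that is the same in both sexes (0 to 0.30).

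**Formulas.** Power of a correlation test in a group of size n, by Fisher z with d = atanh(r) × √(n − 3):

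power = Φ(d − 1.96) + Φ(−d − 1.96).

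Men and women are independent samples, so with powers a and b

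P(exactly one sex significant) = a(1 − b) + b(1 − a).

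**One case in full: 200 women, 100 men, r = 0.20.** atanh(0.20) = 0.2027. In women d = 0.2027 × √197 = 2.845, power 0.812. In men d = 0.2027 × √97 = 1.997, power 0.515. Women only: 0.812 × 0.485 = 0.394. Men only: 0.515 × 0.188 = 0.097. Exactly one: 0.491.

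**All cases, probability that exactly one sex is significant although the association is identical:**

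| Split | r = 0 | 0.10 | 0.15 | 0.20 | 0.25 | 0.30 |
|---|---|---|---|---|---|---|
| 150/150 | 9.5% | 35% | 49% | 43% | 22% | 7% |
| 200/100 | 9.5% | 36% | 52% | 49% | 31% | 14% |
| 225/75 | 9.5% | 37% | 56% | 57% | 42% | 26% |

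**Comparison with a direct test.** In 20,000 simulated studies with r = 0.20 in both sexes, exactly one sex was significant in 43% (150/150) and 49% (200/100). A direct Fisher z comparison of the two correlations rejected in 5.0% and 4.8%, which is its nominal level.

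**Power of the direct test.** The difference in Fisher z detectable with 80% power is (1.960 + 0.842) × √(1/(n₁ − 3) + 1/(n₂ − 3)):

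- 150/150: 2.802 × 0.1166 = 0.33
- 200/100: 2.802 × 0.1240 = 0.35
- 225/75: 2.802 × 0.1356 = 0.38

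For scale, if r is 0.20 in one sex, an upward difference of 0.327 (150/150) means tanh(0.2027 + 0.327) = 0.49 in the other.

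**The case against.** The strongest reply has three parts.

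First, the sentence in section 2.4 does not stop at disaggregation: it also commits to analysing differences. A reader who takes only its first half might infer that the plan does nothing but split the data. That goes too far. What stands is that the second half names no method.

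Second, the article nowhere says that a sex difference will be claimed when one sex is significant and the other is not. A reader might infer from the table that the plan will report false sex differences at those rates. The document does not support this: the percentages describe discordant significance, which becomes a false claim only if it is read as a difference. The table also depends on r. Values near 0.15 to 0.20 are close to the peak, and the rate is much lower at 0.30 or at zero.

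Third, this is a condensed journal article of a descriptive study that says it will generate hypotheses. Model terms are often left to a fuller plan, disaggregated reporting is compatible with a formal test, and the regression sentence leaves room for an interaction. This lowers the weight of the point but does not remove it. The article names a method for each type of comparison, and for a stated main question what it names does not answer that question.

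**Conclusion.** The point holds in a limited form. Main objective 2 asks for sex differences in associations, and section 2.4 offers disaggregation and an undefined gender perspective, neither of which tests such a difference. Objective 1 is not affected, since differences in level between the sexes are covered by the two-category tests.

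If sex-specific p-values are compared, an identical association would appear in one sex only in about 22% to 57% of comparisons for r between 0.10 and 0.25, 7% to 26% at r = 0.30, and 9.5% with no association, against about 5% for a direct test. These figures rest on the assumed correlations and splits.

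Two further inferences should be resisted. Nothing says that whole-sample analyses are dropped, so the plan cannot be said to halve the sample for the overall associations. And although the Introduction and Discussion list being a woman as a risk factor for persistent COVID, no sex ratio is given for this sample. An excess of women is plausible, and would tilt discordant results towards women only (39% against 10% at 200/100 and r = 0.20), but it remains an assumption. The finding does not need it: the rates at 150/150 are already well above 5% for r from 0.10 to 0.25.

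This should be corrected before analysis. It does not undermine the design or the data collected.

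**What to change.** Add to section 2.4, for objective 2, wording to this effect: *Associations are estimated in the whole sample with adjustment for sex. A difference between the sexes in an association is tested by a sex-by-factor interaction term in the linear or logistic model and reported with its 95% CI. Sex-specific estimates are presented as descriptive, and no sex difference is concluded from separate p-values in men and women.*

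The cost is a short paragraph and one extra term in models already planned, with no new data. The downside is power: with 300 participants the direct comparison of correlations reaches 80% power only for a Fisher z difference of about 0.33 to 0.38, so fewer sex differences will be declared and a non-significant interaction will not show that the sexes are alike. The article should state this limit, and the confidence intervals should carry the interpretation.

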## 3 Discussion

The aim of this study is to analyse the vascular structure, the vascular function and biomarkers of endothelial damage in subjects diagnosed with persistent COVID. Moreover, we will conduct a comprehensive analysis of the health of the individuals affected by persistent COVID, examining their quality of life, fatigue, dyspnea, attention capacity, fragility, sleep, and state of anxiety or depression, using validated scales. We will also investigate the influence of the different lifestyles on the evolution of this disease, as well as the degree of vascular ageing caused by persistent COVID.

Persistent COVID is a new entity, for which different terms and multiple definitions have been used (Lopez-Leon et al., 2021; Mandal et al., 2021; Abrignani et al., 2022; Sugiyama et al., 2022). Due to this variability, the absence of a standardised definition and the lack of gathered data, no reliable prevalence data are available. Similarly, the symptoms are very heterogeneous, affecting the multiple organs and systems (Stein et al., 2022; Romero-Rodríguez et al., 2023; Zeng et al., 2023). Although up to 203 symptoms have been identified (Abrignani et al., 2022), the most common symptoms are: fatigue, dyspnea, chest pain, muscle pain, anxiety, headache with reduced functional capacity, and affectation of the quality of life (Stein et al., 2022; Romero-Rodríguez et al., 2023; Zeng et al., 2023). It has been reported that these symptoms, after the acute phase, decrease during the first month, although then they tend to stabilise and, over time, the physical symptoms improve, but not the neuropsychiatric symptoms, which show greater prevalence in the long term (Alkodaymi et al., 2022). Other authors have also identified risk factors for the development or persistent COVID, such as being a woman, initial severity and comorbidities (Tsampasian et al., 2023), as well as protection factors, such as being vaccinated (Azzolini et al., 2022; Kuodi et al., 2022) and following healthy lifestyles before the acute infection (Wang et al., 2023).

Likewise, Lambadiari et al. (2021) published the results of a study with 70 patients, in which those diagnosed with COVID-19 presented persistent AS and endothelial dysfunction at least 4 months after the initial infection, suggesting a long-term impact on patients with persistent COVID both in AS and in endothelial function (Ikonomidis et al., 2022). However, cfPWV did not vary with the severity of COVID-19, which indicates that vascular dysfunction persists regardless of the initial severity of the disease, although this hypothesis must be confirmed in larger cohorts (Mavraganis et al., 2022; Zota et al., 2022). It is also known that COVID-19 infection invades endothelial cells (endotheliitis) (Varga et al., 2020), and the subsequent endothelial dysfunction is associated with a bad result (Zota et al., 2022). As such, the endothelium plays a double role in the physiopathology of COVID-19: a target organ for the infection and a mediator in the subsequent inflammatory and thrombotic cascades (Mavraganis et al., 2022; Zota et al., 2022). This endothelial dysfunction may extend beyond the acute phase and influence the prognosis of persistent COVID (Lambadiari et al., 2021). Thus, in a study with a 12-month follow-up (Ikonomidis et al., 2022), it was found that the patients with COVID-19 presented persistent AS and endothelial dysfunction. Moreover, we can currently evaluate both central and peripheral AS in a non-invasive manner (Boutouyrie and Vermeersch, 2010; Munakata, 2016; Namba et al., 2019). Therefore, the European Society of Cardiology states that an exhaustive monitoring and further research are necessary to address the possible therapeutic and prognostic implications of endotheliitis induced by COVID-19, recommending an evaluation of AS as a marker of the result of COVID-19 (Evans et al., 2020). In this sense, authors such as Saeed et al. point out that COVID-19 infection and AS have a bidirectional cause-effect association (Saeed and Mancia, 2021). Lastly, it is important to highlight that the number of patients included in the studies that analyse these aspects is small; thus, further research is necessary to determine the impact of persistent COVID on AS and on vascular ageing.

In conclusion, persistent COVID is emerging as an important public health problem. Currently, there are many questions to answer: it is still unclear what the prevalence is, how the symptoms will evolve in the long term, and what the rate will be in people infected after the vaccinations and in those affected by the different variants of SARS-CoV-2 (e.g., Delta, Omicron). Moreover, the literature suggests that COVID-19 causes early vascular ageing and increased AS. However, it is not clear whether this vascular alteration affects the entire vascular tree. Therefore, measuring AS in the whole vascular tree (central and peripheral), which will be carried out in this study, will help to improve our understanding of the vascular affectation of COVID-19, and its prognostic importance will help to characterise it in its entirety, which is an essential step in the management of its evolution. Moreover, it is necessary to perform studies that analyse the reversibility of the vascular changes induced by COVID-19 and their impact on the prognosis in the long term, taking into account that the new and emerging variants could have different effects.

The main limitations of this study should also be highlighted. Firstly, the participants will not represent a random sample of the population diagnosed with persistent COVID. Secondly, due to the cross-sectional nature of the study, it will not be possible to infer causality, although it will allow analysing the associations and generate hypotheses for future prospective studies. On the other hand, the project has strengths that must be underlined, such as the fact that this will be the first study in a Spanish population to analyse the alteration in vascular structure and function, as well as vascular ageing, in patients diagnosed with persistent COVID, exploring the determinants of this disease, as well as the possible role of the inflammatory process in it. In turn, the study will also allow analysing the quality of life of these patients, including the physical, psychological and cognitive aspects, for a better primary care, providing clues for future interventions in the daily care practice. It is also worth mentioning the role of the patients, i.e., those directly affected by persistent COVID, since their role will be key in their visibility and recognition, and they will actively participate in the project through focal discussion groups, in which we will analyse the opinions and experiences of the affected population.

## 4 Brief summary

Persistent COVID is an entity that affects a high percentage of people infected with SARS-CoV-2. This virus can infect the vascular endothelium, which, in turn, causes endothelial alterations that are related to arterial stiffness. Therefore, it is necessary to study the relationship between persistent COVID and the alterations in arterial stiffness. Thus, we propose this study, which is aimed at analysing vascular structure, function and ageing in Spanish adults diagnosed with persistent COVID, determining the differences between sexes. Moreover, it is important to analyse the association of the clinical symptoms, body composition, lifestyles (physical activity, diet, consumption of alcohol and smoking habits), psychological and cognitive factors and inflammatory factors with vascular structure, function and ageing, determining the differences between sexes. The identification of potential risk factors will help to detect people at greater risk of developing persistent COVID, which will enable an early and appropriate clinical support. Furthermore, it is not clear whether the vascular alterations caused by COVID-19 are resolved after the acute infection or remain over time, favouring the increase of arterial stiffness and early vascular ageing. Consequently, it is necessary to propose studies that analyse the evolution of this disease in this group of patients, as well as the possible variables that influence it.

